**Figure 1 F1:**
[figure not shown]
Randomization flow chart.

### Eligibility

Studies in the chronic and early subacute phase post-stroke have consistently demonstrated the adaptability and flexibility of the *NJIT-RAVR* robotic/VR system, thus allowing for broad inclusion criteria (36, 37). We are including subjects 30–90 years old, able to follow instructions, with severe to moderate arm weakness (≥10/66 and ≤49/66 FM score), and intact cutaneous sensation. Individuals with UEFMA scores <10 will not be included as they will not have the motor ability to utilize the system effectively. Patients will be excluded from the study if they were not independent prior to the stroke, are too ill to tolerate training, have persistent motor impairment from prior stroke, have aphasia or spatial neglect precluding their performing the tasks or following task instructions, have ≥1 on the NIHSS limb ataxia item, severe proprioceptive loss, ≥3 on the Modified Ashworth Scale (of the elbow, wrist, or finger flexors), or a previous medical history of neurological deficits or orthopedic conditions that limit arm and hand movement.

### Interventions

The *NJIT-RAVR* system (38), developed by our group, is a haptic robot integrated with a library of virtually simulated rehabilitation interventions. The system will be used for the early (initiated 5–30 days post-stroke) and late (initiated 30–60 days post-stroke) intensive VR/Robotic therapy groups. This system consists of a data glove, and the Haptic Master, which is a 3 degrees of freedom admittance-controlled robot combined with a 3 degrees of freedom gimbal. The robotic arm tracks the hand in a 3D workspace and enables haptic effects, that include, springs, dampers, and other assistive and resistive forces as well as haptic objects, such as walls, floors, tables, and complex-shaped objects for hand manipulation. Th*e NJIT-Track Glove* system is an instrumented glove that tracks finger angles, a robotic hand exoskeleton that provides assistance/resistance to fingers and a three-dimensional tracking system to track hand position and orientation. Using programmable software and custom bracing of the end effector we enable use of this system for patients with a broad set of impairments and functional abilities. A library of impairment and task-based simulations have been developed. The simulations are designed to train proximal arm transport and wrist and finger manipulation. The simulations train the upper extremities either together or separately (36, 39) and include activities such as using individual fingers to play a virtual piano, extending fingers to hit a ball, transporting the arm to eliminate spaceships, using a pinch grasp to move a monkey onto higher and higher branches, integrating reach and grasp to lift virtual cups of various weights onto a haptic shelf placed at a variety of heights, and integrating reach and forearm pronation and supination to hammer a nail into a piece of wood. The subjects will participate in this training 1/h per weekday (total of 10 h).

There are three experimental groups and one comparator group. The Early Robotic/VR Therapy (EVR) experimental group will receive state-of-art inpatient usual care therapy plus an extra 10 h of intensive therapy focusing on the hand using robotically facilitated rehabilitation interventions presented in virtual environments and initiated 5–30 days post-stroke. The Delayed Robotic/VR Therapy (DVR) experimental group will receive state-of-art usual care therapy (inpatient and outpatient) plus an extra 10 h of intensive therapy focusing on the hand using robotically facilitated rehabilitation interventions presented in virtual environments and initiated 30–60 days post-stroke. The dose-matched usual care group will receive an extra 10 h of usual care physical/occupational therapy focusing on increasing range of motion, strength, and functional use of the hand. Therapists providing the dose-matched interventions will follow the same protocol the subjects receive during their usual care, and this is initiated 5–30 days post-stroke. A comparator group will receive state-of-art usual care consisting of a combination of physical, occupational, and speech therapy for 3 h each day as prescribed by Kessler Institute for Rehabilitation (KIR) physicians and regulated by the Centers for Medicare and Medicaid Services. UC consists of adaptive and progressive task and impairment based therapy including strengthening, ROM for the affected upper and lower extremity, mobility (bed mobility, transfers, gait, and elevations), and activities of daily living (dressing, toileting, meal preparation). Subjects with finger and wrist weakness typically also receive electrical stimulation of the finger and wrist extensor muscles. The same program of interventions is provided to members of the other three groups.

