### Study Aims and Hypotheses

This study is designed to empirically test the controversy regarding both the value of intensive, high dosage training as well as the optimal timing for intensive VR/Robotic training in the first 2 months after stroke. We are continuing an ongoing investigation into the effects of intensive task and impairment-based training of the hemiparetic upper limb with a focus on the hand using robotically facilitated rehabilitation interventions presented in virtual environments. The primary aim of this study is to test, at 4 months post-stroke, whether adding intensive VR/Robotic motor training to a patient's standard of care rehabilitation at 5–30 days post-stroke, improves functional outcomes of the hemiparetic hand when compared to initiating the additional VR/Robotic motor training 30–60 days post-stroke; thus testing the concept of optimal timing. Other comparisons include comparing Early VR to dose-matched usual care to test the potential benefits of the high-intensity VR/Robotic intervention. Comparing dose-matched usual care (10 additional hours of standard therapy) to usual care (no additional therapy) will inform about the benefits of increased dosing (Table 1). See controversies elucidated in recent literature (12, 30). We hypothesize that the outcomes will favor the early, high dosage VR/Robotic hand training group when compared to the delayed VR/Robotic training group and dose matched usual care group. The secondary aims will systematically investigate the mechanisms underlying the changes resulting from early timing of training and increased dosing, specifically changes in kinematics, kinetics, patterns of cortical somatotopic reorganization, and brain connectivity. We further hypothesize that the early, high dosage VR/Robotic hand training group will show a larger relative contribution of restored kinematic motor patterns to the overall improvement in motor function and these functional gains will be associated with the expansion of ipsilesional hand cortical somatotopy.

**Table 1 T1:** Comparison groups.

**Group comparisons**	**Intervention period^**+**^**	**Test**
EVR vs. DVR^*^	5–30 vs. 30–60 days	Timing of a VR/robotic intervention
EVR vs. DMUC^**^	5–30 days	VR/Robotic vs. conventional intervention
DMUC vs. UC^***^	5–30 days	Dosing of an intervention

* Early Virtual Reality vs. Delayed Virtual Reality,

** Dose Matched Usual Care,

*** *Usual Care; ^+^Time Post-Stroke*.

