### Randomization and Recruitment

An independent statistician will generate the randomization sequence prior to initiation of the study. Physicians and therapists will identify potential subjects. The study coordinator will contact the patients as soon as they are medically stable, inform them about the study, screen them for inclusion and exclusion criteria and enroll them. The subjects will be stratified on two dimensions, impairment level and presence or absence of Motor Evoked Potentials (MEPs). Prior to randomization, potential subjects will be assessed using the Upper Extremity Fugl-Meyer Assessment (FM) (33) to establish motor impairment level, and Transcranial Magnetic Stimulation (TMS) for the presence or absence of MEPs in the lesioned hemisphere. These scores will be used to stratify subjects into four subgroups; (1) Severe, FM score 10–19, MEP+, (2) Severe, FM score 10–19, MEP–, (3) Moderate, FM score 20–49, MEP+, (4) Moderate, FM score 20–49, MEP-. If a subject is not eligible for TMS, he/she will be assigned to either group 2 (if severe) or group 3 (if moderate). This is based on the Stinear et al. (34) study in which study subjects with moderate impairment all had MEPs (34). Stratified block randomization will then be used to achieve a balanced assignment (35). For each of the four subgroups, every 4 subjects are one block. In each block, there is one subject for each type of treatment. One hundred twenty subjects will be assigned sequentially to four types of treatment groups (30 per group): (a) state-of-art usual care only (UC), (b) usual care plus an additional 10 h of usual care (dose-matched usual care, DMUC; initiated 5–30 days post-stroke), (c) usual care plus an additional 10 h of intensive therapy focusing on the hand using robotically facilitated rehabilitation interventions presented in virtual environments initiated **early** (5–30 days post-stroke) (EVR), and (d) usual care plus an additional 10 h of intensive therapy focusing on the hand using robotically facilitated rehabilitation interventions presented in virtual environments initiated later (30–60 days post stroke) (DVR) (see Figure 1).

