### Measures

There are several types of outcome measures in this study: clinical measures, neurophysiological measures, kinematic/kinetic measures, a measure of daily use of the hemiplegic extremity, and a quality of life measure. For the clinical measures, a therapist blinded to group assignment will perform all outcome assessments. For the EVR and DMUC groups, the measures will be taken immediately prior to intervention (ideally within 72 h), immediately post-intervention (ideally within 72 h), 1 month post-intervention, and 4 and 6 months post-stroke. For the DVR group, there will be an additional measurement taken immediately post-enrollment (ideally within 72 h). For the UC group, the measures will be taken immediately post-enrollment (ideally within 72 h), 2 weeks post the first test, 1 month post the second test and 4 and 6 months post-stroke.

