### Sample Size

For Aim 1, the planned primary analysis method is a mixed effect model. The primary outcome measure is the change in ARAT score from baseline evaluated at 4 months post-stroke. The estimated effect size for the interaction term is 0.42 (Cohen's f), and the estimated within-subject correlation is 0.7. For testing the hypothesis of Treatment Group (EVR, DVR, UC, DMUC) ^*^Test Time (Baseline, 4 M post-stroke, 6 M post-stroke) effect, and assuming compound symmetry correlation for within-subject measurements, for significance level 0.05, a total of 84 patients (21 for each group) are needed to detect the overall Treatment Group ^*^ Test Time interaction effect. But for the main planned contrasts, Treatment Group (EVR, DVR) ^*^ Test Time (Baseline, 4 M post-stroke) and Treatment Group (UC, DMUC) ^*^ Test Time (Baseline, 4 M post-stroke), a total of 96 patients (24 for each group) are required to detect the effect size of 0.42 between EVR and DVR or between UC and DMUC over time. Since detecting these contrasts is the main goal of the study, at least 96 subjects, 24 subjects per group, are required. After taking into account subject attrition, our total sample size will be equal to 120. We plan to run an interim analysis and update the sample size when we have recruited 50% of subjects.

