We will use the robust mixed effect model approach to analyze the data. We demonstrated in the past that this analytic approach is robust to detect treatment effects, even with relatively small groups of patients in whom within-group variance occurs with respect to stroke characteristics (56). Test Time (Pre, Post, 1-month post-treatment, 4 months post-stroke, 6 months post-stroke) and Treatment Group (EVR, DVR, DMUC, UC) will be treated as fixed effects in the mixed models. The interaction term between Test Time and Treatment Group will be included. Baseline measurements will be added as a covariate into mixed models for outcome variables. Random intercept will be used to model subject-level variation. Covariance pattern and model selection will be implemented with likelihood-based tests. Contrasts to compare group means will be applied to obtain comparisons between time, and between treatments, with multiplicity adjustment considered. We have an a priori interest in specific Test Time by Treatment Group interaction effects for the EVR-DVR, for the DMUC-UC, and for the EVR-DMUC comparisons. The particular differences we are interested in are Pre vs. Post and Pre vs. second (4 months post stroke) retention assessments. In the case of balanced data and equal variances, we will use the Tukey procedure to test for significant interaction effects, otherwise, Bonferroni correction will be used. In our design, the timing comparison is the difference between EVR and DVR. The dosage comparison is the difference between UC (usual care) and the DMUC (usual care plus 10 additional hours). In addition, we will be able to compare the type of training effect, VR vs. dose-matched usual care (EVR vs. DMUC), where both types of training are delivered in the same time period.

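### The early and delayed start windows share day 30 with no minimum per-patient gap, and the stated model leaves out days since stroke: two minor, cheaply mended weaknesses in the timing contrast

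*Protocol article*

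**What the plan says.** The Interventions section describes the "early (initiated 5–30 days post-stroke) and late (initiated 30–60 days post-stroke) intensive VR/Robotic therapy groups". The abstract, Table 1, Randomization and Recruitment and Statistical Analysis give the same day ranges. The article states no minimum interval between randomisation and the DVR start, and no enrolment cut-off before day 30. On course length it says "The subjects will participate in this training 1/h per weekday (total of 10 h" in all).

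Study Aims and Hypotheses makes EVR versus DVR at 4 months post-stroke the primary comparison, "thus testing the concept of optimal timing".

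Two statements bear on how late patients enter and how far apart the arms are. Under Randomization and Recruitment, "The study coordinator will contact the patients as soon as they are medically stable". Under Interventions, EVR is added to inpatient usual care, and DVR to inpatient and outpatient usual care. Table 2 notes that DVR has two pre-tests, one in hospital and one just before its training.

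On the analysis, Sample Size says "The primary outcome measure is the change in ARAT score from baseline evaluated at 4 months post-stroke". For EVR and DMUC, Measures says "the measures will be taken immediately prior to intervention (ideally within 72 h"), so the calendar position of the first assessment varies between patients. In Statistical Analysis, Test Time and "Treatment Group (EVR, DVR, DMUC, UC) will be treated as fixed effects in the mixed models", with their interaction and a random intercept, and "Baseline measurements will be added as a covariate into mixed models for outcome variables". Time since stroke is neither a named covariate nor a stratification factor; the factors are impairment level and MEP status.

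**The concern.** In a trial whose main question is when to start, the start-day rule defines the treatment contrast. If a patient enters on day 29, the rule permits an EVR start that day and a DVR start on day 30. That patient contributes almost nothing to a comparison of timing. If there were many such patients, the EVR–DVR difference would shrink toward zero. A null result could then mean either that timing does not matter or that the arms trained at similar times.

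The second part concerns precision. A patient first assessed on day 5 has more of the recovery period ahead before the 4-month visit than one first assessed on day 28. Entry day is therefore plausibly prognostic for the change score, even at the same baseline ARAT. It is known before allocation, so adjusting for it is legitimate and nearly free.

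**Working it through.** **The plan's own sample size.** Inputs from Sample Size: f = 0.42, alpha 0.05, 24 per group for a two-group, two-time contrast. Power is not stated; 80% is assumed here.
- Noncentral F with λ = f²N = 0.1764 × 48 = 8.47 on 1 and 46 df gives 81.3%. With 23 per group it gives 79.6%, so 24 per group is reproduced.
- For the overall interaction (four groups, three times), 21 per group gives 82.1% and 20 gives 79.7%, so 84 in total is reproduced.
- 96/(1 − 0.20) = 120, which corresponds to 20% attrition.
- The same contrast as a two-sample t-test on change has d = 2f = 0.84 and noncentrality 0.84 × √(24/2) = 2.91, again 81.3%.

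**What the windows permit.** For a patient randomised on day r who could start EVR at once, the smallest gap to a permitted DVR start is 30 − r days: 25 at r = 5, 10 at r = 20, 2 at r = 28 and 0 at r = 30. The largest is 60 − r. Ten weekday sessions span 12 calendar days from a Monday start and 14 from any other weekday. So for anyone randomised after day 16, a DVR start inside the span of that patient's would-be EVR course is allowed.

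**How often, under assumed distributions.** Take EVR start = entry day, uniform on days 5–30, and DVR start uniform on days 30–60, independent.
- Mean gap = 45 − 17.5 = 27.5 days.
- P(gap < 14) = (14²/2)/(25 × 30) = 98/750 = 13%. P(gap < 12) = 72/750 = 10%.
- With entry on days 5–20 instead, P(gap < 14) = (4²/2)/(15 × 30) = 8/450 = 2%.

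**Effect of a minimum-gap rule on power.** Assume that d = 0.84 belongs to a 27.5-day gap and that benefit is proportional to the mean gap. The rule is DVR start = max(drawn start, 31, entry + 17), simulated with 4,000,000 draws.

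| Entry days | DVR starts | Mean gap before → after | Power before → after | DVR starts moved |
|---|---|---|---|---|
| 5–30 | 30–60 | 27.5 → 28.6 | 81.3% → 84.2% | 20%, by 5.4 days on average |
| 5–20 | 30–60 | 32.5 → 32.6 | 92.0% → 92.2% | 7%, by 1.9 days on average |

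For the first row, d after the rule = 0.84 × 28.6/27.5 = 0.874, and the noncentrality is 0.874 × √12 = 3.03.

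**Why 17 days.** Suppose EVR begins within 72 h of randomisation, moved to the next weekday if that falls on a weekend. Enumerating all seven randomisation weekdays, the tenth session falls at the latest on day r + 16. An example is randomisation on a Wednesday, first session the following Monday (r + 5) and tenth session on the Friday of the next week (r + 16). A DVR start on r + 17 therefore clears it. Fourteen days would be enough only if EVR began on the day of randomisation. The latest start that the rule can force is 30 + 17 = day 47.

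**Covariate.** If entry day explains a share R² of residual variance, the effective d is 0.84/√(1 − R²). At 24 per group:
- R² = 0.02: d = 0.849, power 82.1%.
- R² = 0.05: d = 0.862, power 83.2%.
- R² = 0.10: d = 0.885, power 85.1%.

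R² cannot be obtained from the document; 2–10% is an assumed range.

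**The case against.** The strongest reply is that the arms are separated by care setting as well as by days. EVR is given during the inpatient stay. Anticipated Results and the Discussion ask whether therapy begun right after discharge does as well. A patient randomised on day 29 would need an inpatient course running to about day 42, while the Discussion speaks of shrinking lengths of stay. Contact at medical stability also points to early entry. This largely stands: it makes near-coincident starts an edge case. It does not remove them, because the setting fixes no number of days.

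A second reply is that further covariates are usually left to the SAP. That is fair as far as it goes, and the SAP may already include entry day. The article does write the model out, though, so naming one more covariate is a concrete improvement to a stated model. It does not correct an error.

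Three stronger readings are tempting, and the document supports none of them.
- A reader might infer that the shared day invalidates the timing comparison. The overlap is one boundary day, and no entry-day data suggest that many patients sit near it.
- A reader might infer a serious loss of power. If DVR starts fell only on days 30–45 with uniform entry on days 5–30, the mean gap would be 20.0 days and power about 54%. Nothing in the article confines DVR starts in that way or ties f = 0.42 to a particular gap. The Introduction stresses the first month as a critical period, which is not a linear benefit per day.
- A reader might infer that omitting days since stroke biases the result. Randomisation balances it in expectation, so only precision is lost.

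**Conclusion.** The point holds as a minor one. The windows do allow a patient entering late to receive nearly the same treatment timing in either arm, and nothing stated rules it out. Its frequency is unknown and probably low. Under the stated windows a minimum-gap rule is worth about 0 to 3 power points, given uniform start days, benefit proportional to the gap, and f = 0.42 attached to a 27.5-day gap. The missing covariate is worth about 1 to 4 points at 24 per group if entry day explains 2–10% of residual variance. Neither part makes the planned sample size wrong. The main practical gain is a cleaner reading of a null timing result.

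**What to change.** 1. Add days from stroke to randomisation, and its product with Test Time, to the model in Statistical Analysis. The trial must already hold this value to apply its windows. The cost is one degree of freedom plus one for each test time beyond the first (four with the five times listed). This is a free improvement.

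2. Optionally, for patients still to be enrolled (Current Results reports seven who had completed follow-up), start DVR no earlier than day 31 and at least 17 days after randomisation. This keeps the delayed course clear of an EVR course begun within about 72 h of randomisation. If EVR routinely starts later than that, the interval should be lengthened to match. The latest forced start is day 47, inside the existing window. The cost is scheduling only: about 20% of DVR starts would move later, by about 5 days on average, with uniform entry on days 5–30, or about 7% by about 2 days with entry on days 5–20. No extra patients, visits or procedures are needed.

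In either case, report the start-day separation actually achieved and read a null timing result in its light.

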### Measures

There are several types of outcome measures in this study: clinical measures, neurophysiological measures, kinematic/kinetic measures, a measure of daily use of the hemiplegic extremity, and a quality of life measure. For the clinical measures, a therapist blinded to group assignment will perform all outcome assessments. For the EVR and DMUC groups, the measures will be taken immediately prior to intervention (ideally within 72 h), immediately post-intervention (ideally within 72 h), 1 month post-intervention, and 4 and 6 months post-stroke. For the DVR group, there will be an additional measurement taken immediately post-enrollment (ideally within 72 h). For the UC group, the measures will be taken immediately post-enrollment (ideally within 72 h), 2 weeks post the first test, 1 month post the second test and 4 and 6 months post-stroke.

### Primary Outcome

The primary clinical outcome for this study is the Action Research Arm Test (ARAT) (40). Four subscales in this 19-item test measure the following upper extremity activities; grasp (6 items), grip (4 items), pinch (6 items), and movement 3 items). Each item is rated on a four-point scale with the following values, 0 = no movement, 1 = the movement task is partially performed, 2 = the movement task is completed but takes abnormally long, and 3 = normal movement. Scores range from 0 to 57 with higher scores indicating better performance.

